### Cost-effectiveness analysis

#### Costs

Three types of costs will be included: (1) healthcare costs including intervention costs (i.e. rTMS, pharmacotherapy, CBT sessions), (2) patients’ and their family’s costs for travel and informal care, and (3) costs stemming from productivity losses due to absenteeism and lesser efficiency while at work, both in paid work and volunteer jobs. Data on resource use (health care uptake, informal care, travel distances to health services, and productivity losses) will be collected with the latest version of the Trimbos/iMTA Questionnaire on Costs associated with Psychiatric illness (TiC-P) [43]. Total costs will be estimated using a bottom-up (or micro-costing) approach, where units of healthcare usage are multiplied by their appropriate unit cost price and summed to provide an overall total cost estimate [44]. Unit cost prices will be obtained from the latest Dutch guideline for health economic evaluation. Costs of medication (and the pharmacist’s dispensing costs) will be calculated using prices based on Daily Defined Dosage (DDD) taken from www.farmacotherapeutischkompas.nl and www.medicijnkosten.nl. Productivity losses will be based on the friction cost method as per the Dutch guideline. Costs of transport will be calculated as the mean distance per destination multiplied by standard cost prices. If needed, cost prices will be indexed to 2021 using the consumer price index from Statistics Netherlands.

#### Effects

For the CEA, the central clinical end-term will be remission defined as a HDRS-17 depressive symptom severity of less than 8 at 6 months follow-up. For the CUA, the Dutch tariffs of the EQ-5D-5L will be used for computing QALYs [45]. Cumulative costs and QALY gains over the study’s follow-up period will be computed with the area under the curve method. A second CEA will be performed based on the subgroup of patients for which extended follow-up data up until 12 months is available.

#### Combining costs and effects

The comparability of groups at baseline will be assessed for both costs and outcomes, and covariates will be used for adjustment if needed. Missing cost and outcome data will be imputed using multiple imputation with chained equations (MICE) for intention-to-treat (ITT) analysis. Since the trial’s follow-up does not exceed 1 year, no discounting will be performed. The incremental cost-effectiveness ratio (ICER) will be computed to obtain the incremental costs per remitter and the incremental costs per QALY gained. Stochastic uncertainty will be handled using 5000 non-parametric bootstraps and by plotting simulated ICERs on the ICER plane. For decision-making purposes, the ICER acceptability curve will be plotted for various willingness-to-pay (WTP) ceilings for making judgments whether the rTMS added to CBT and antidepressants offers good value for money relative to CBT and switching of antidepressants alone. One-way sensitivity analyses directed at uncertainty in the main cost drivers and outcomes will be performed to assess the robustness of our findings (e.g. under different imputation strategies, e.g. multiple imputation using estimation-maximalization (MIEM)). Both the analysis and reporting of the findings will adhere to the (extended) CONSORT and CHEERS statements [46–48].

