## Methods

### Study design

In this pragmatic randomized controlled trial (RCT), patients are randomly assigned to one of two treatment conditions. In the first condition, treatment consists of rTMS combined with CBT and continued antidepressant medication, which will hereafter be referred to as the rTMS arm. In the second condition, treatment consists of a switch from the current antidepressant medication to a tricyclic antidepressant (TCA) or augmentation with lithium or a second-generation antipsychotic, also in combination with CBT. This will be referred to as the medication arm. The trial consists of 8 weeks of unblinded treatment followed by a follow-up of the cohort at four and 6 months from baseline onward. For a subgroup of the patients, an extended follow-up will take place at nine and 12 months from baseline onward to assess effect decay or preservation. See Fig. 1 for the CONSORT flowchart. Patients in the medication arm who did not recover to the medication intervention can receive rTMS after completion of the first 8 weeks of treatment.

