### Procedure

This is a multicenter trial, taking place within the Dutch specialized mental health care setting. Patients are recruited and treated at Radboud University Medical Center (Radboudumc; Nijmegen), Pro Persona mental health care (Nijmegen, Arnhem), neurocare (Nijmegen, Arnhem, Eindhoven, Den Haag), the Elisabeth TweeSteden Hospital (ETZ; Tilburg), GGZ inGeest mental health care (Amsterdam), the St. Antonius Hospital (Utrecht, Nieuwegein), and also recruited via the Dutch Depression Foundation. If patients are eligible for participation, the psychiatrists or psychologists approach them to participate in the trial, after which they are contacted by a researcher. Study information is provided and patients are contacted again after at least 24 h to discuss participation and discuss any remaining questions. If patients decide to participate, they are invited for a research intake, where they are asked to sign the informed consent form and all baseline measurements are conducted. Afterwards, patients are randomized by the principal investigator (see below).

At baseline and during treatment, questionnaires will be administered by the clinician or researcher. Patients also fill in questionnaires themselves, which are sent via email using the secure online data capture program for clinical trials, Castor EDC [33]. The questionnaires can be filled out via any personal device (e.g. computer, tablet, smartphone). The expected study duration is 39 months, and inclusion of patients started in August 2019.

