### Secondary objective - health-related quality of life and healthcare costs

To measure (changes in) health-related quality of life of the patients the EuroQol 5-dimensions 5-levels (EQ-5D-5L) will be used. The EQ-5D-5L describes health states over five domains (mobility, self-care, usual activities, pain/discomfort and anxiety/depression) and can be completed in less than 5 min. Dutch tariffs will be applied to each of the health states to obtain utilities, which are anchored at 0 (death) and 1 (full health). EQ-5D-5L utilities will be combined over time using the area under the curve (AUC) method to capture the cumulative QALY health gains over the entire six- or twelve-month follow-up period.

The Trimbos Institute and iMTA Cost questionnaire for Psychiatry (TiC-P) will be used for measuring health care usage (and the costs thereof), patients’ and their family’s out-of-pocket costs, and productivity losses owing to absenteeism and presenteeism. In the Netherlands the TiC-P is the most frequently used health care receipt questionnaire for health-economic evaluation. Completion of the TiC-P will take roughly 10 min.

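### Baseline adjustment of QALYs and costs is left to an inspection of balance, with no criterion and no named covariate, although baseline utility is part of the QALY area under the curve

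*Protocol article*

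**What the plan says.** In the protocol article, under Combining costs and effects, the rule is: "The comparability of groups at baseline will be assessed for both costs and outcomes, and covariates will be used for adjustment if needed". Uncertainty is covered in the same section: "Stochastic uncertainty will be handled using 5000 non-parametric bootstraps". The sensitivity analyses listed there concern cost drivers, outcomes and imputation; none is described as baseline-adjusted.

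The section on health-related quality of life and healthcare costs defines the QALY: "EQ-5D-5L utilities will be combined over time using the area under the curve (AUC) method to capture the cumulative QALY health gains", taken "over the entire six- or twelve-month follow-up period". The Effects section repeats this: "Cumulative costs and QALY gains over the study’s follow-up period will be computed with the area under the curve method". Neither passage has a baseline term.

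Under Procedure, the research intake is where "all baseline measurements are conducted", and randomisation follows. Under Study design: "The trial consists of 8 weeks of unblinded treatment followed by a follow-up of the cohort at four and 6 months from baseline onward".

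The clinical analysis is handled differently. The sample size section rests on a repeated-measures ANCOVA that takes credit for a baseline to follow-up correlation of 0.59, and the section on change in depression severity fixes age and gender as covariates in advance.

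**The concern.** This is a decision rule that the article states, not a detail left to a fuller plan: look at the baseline data, then decide. Three consequences follow.

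- **Precision.** Baseline utility enters the area under the curve directly and is likely to be correlated with every later utility. An analysis that omits it by default gives up precision that costs nothing to obtain.
- **Error given the observed imbalance.** Any chance difference in baseline utility passes into the unadjusted QALY difference, whether or not it is large enough to catch the eye.
- **Discretion.** Need is not defined and no covariate is named, so two incremental cost-effectiveness ratios, adjusted and unadjusted, are both available once the data are known. Treatment is unblinded, and the Aims section states the expectation that rTMS will be the more cost-effective option.

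The incremental QALY is the denominator of the cost-utility ratio, so the bootstrap cloud and the acceptability curve inherit these effects. Incremental costs raise the same question of precision and discretion, although I cannot size it because the document gives nothing on the distribution of costs.

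**Working it through.** **The plan's own figure.** The article states no figure for the QALY analysis. Its sample size reproduces. With 5 post-baseline measurements, r = 0.69 between follow-ups, r = 0.59 with baseline and d = 0.33, the variance factor is (1 + 4 × 0.69)/5 − 0.59² = 0.4039. Then n = 2 × 0.4039 × ((1.960 + 0.842)/0.33)² = 58.2, so 59 per arm, and 118/0.9 = 131.1, so 132, or 66 per arm. Nothing below changes this.

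**Inputs for the QALY illustration.**
- 66 per arm: from the document.
- Utility SD 0.25: assumption.
- EQ-5D-5L at 0, 8 weeks, 4 and 6 months: assumption, because the assessment schedule is in a figure that is not shown.
- Correlation 0.69 between follow-up utilities: assumption, borrowed from HDRS-17.
- Correlation r between baseline and follow-up utility: assumption, 0.3 to 0.7. The HDRS-17 value of 0.59 lies inside this range, but it belongs to another scale and to the treatment period.

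**Trapezoid weights** (years): w0 = 0.077 for baseline, then 0.167, 0.173 and 0.083. The follow-up weights sum to W = 0.423 and their squares to 0.0647. Baseline utility carries 0.077/0.5 = 15% of the 6-month area.

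**Formulas**, with utility variance set to 1:
- slope of QALY on baseline utility: c = w0 + r × W
- QALY variance: v = w0² + 2 × r × w0 × W + 0.31 × 0.0647 + 0.69 × W²
- proportion of variance removed by adjustment: c²/v
- shift per 0.05 of baseline imbalance: 0.05 × c
- unadjusted SE: 0.25 × √(v × 2/66)

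**Worked case, r = 0.59.** c = 0.077 + 0.59 × 0.423 = 0.327. v = 0.0059 + 0.0384 + 0.0201 + 0.1235 = 0.188. The correlation is 0.327/√0.188 = 0.753, so adjustment removes 57% of the variance and the SE falls from 0.0189 to 0.0124. The shift is 0.05 × 0.327 = 0.016 QALY.

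**Range over r.**

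| r | c | variance cut | shift per 0.05 | unadjusted SE |
|---|---|---|---|---|
| 0.3 | 0.204 | 25% | 0.010 | 0.0179 |
| 0.5 | 0.289 | 46% | 0.014 | 0.0186 |
| 0.59 | 0.327 | 57% | 0.016 | 0.0189 |
| 0.7 | 0.373 | 71% | 0.019 | 0.0192 |

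For scale, the SE of a chance baseline difference under simple randomisation is 0.25 × √(2/66) = 0.0435, so an imbalance of 0.05 is only a little more than one standard error.

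**Sparser visits.** If utilities were taken only at 0 and 6 months, baseline would carry half of the area. Over the same r, the variance cut would be 65 to 85% and the shift 0.016 to 0.021 QALY.

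**Baseline-subtracted reading.** The article speaks of QALY gains. If that means utilities minus each patient's baseline, the slope is c − 0.5. At r = 0.59 this is 0.327 − 0.5 = −0.173, so the shift is 0.05 × (−0.173) = −0.009 QALY. The variance is 0.188 − 0.327 + 0.25 = 0.111, and the cut is 0.173²/0.111 = 27%. The adjusted SE is 0.0124, the same as before: regression on baseline gives the same answer under either construction, while the unadjusted results differ in both sign and size.

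**The case against.** Much can be said for the plan, and most of it limits the point without removing it.

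- **A reader might infer that the QALY estimate is biased.** It is not, on average: randomisation sees to that. What remains is lost precision and error conditional on the imbalance that occurs.
- **A reader might infer an inflated false-positive rate.** The calculations do not show that. In a simulation that adjusts only when the baseline difference has p < 0.05 (66 per arm, QALY/baseline correlation 0.5 to 0.8), overall type I error was 0.030 to 0.045, which is conservative. Error rose only among trials with a moderate unflagged imbalance (baseline p 0.05 to 0.30): 0.077 to 0.099 unadjusted, against 0.050 to 0.056 adjusted.
- **The article mentions no significance test.** A threshold of imbalance below which adjustment would be skipped cannot be derived from it, and a check by judgement might well lead to adjustment. The lack of any criterion stands as the fault.
- **A reader might infer that the bootstrap ignores the adjustment step.** The article does not say whether adjustment happens inside or outside the bootstrap, and a condensed article may leave that to the full plan.
- **The size rests on assumptions.** The SD, visits and utility correlations are not in the document, so a single percentage would be misleading. Only the range should be used.
- **Stratification by HDRS-17 severity** may make utility imbalance smaller than under simple randomisation. It balances neither EQ-5D-5L nor costs directly.
- **Scope.** The cost-effectiveness analysis uses remission at 6 months, which contains no baseline utility, and the whole evaluation is a secondary objective.

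**Conclusion.** The point holds as one of method. Adjustment of costs and effects depends on an undefined inspection of baseline balance, while baseline utility is built into the QALY. On the plain area-under-the-curve reading, and under the assumptions listed above, always adjusting would cut the variance of the 6-month QALY difference by about 25 to 71%, and would remove a shift of about 0.010 to 0.019 QALY per 0.05 of utility imbalance. If gains are baseline-subtracted, the corresponding figures at r = 0.59 are about 27% and −0.009 QALY. Fixed regression adjustment is the better choice on either reading, and it closes the post-hoc choice between two ratios.

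I am confident of the direction and not of any single figure. The primary analysis and the sample size are untouched, and the consequence falls mainly on the cost-utility analysis.

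**What to change.** Replace the sentence under Combining costs and effects with:

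> Incremental QALYs will be adjusted by regression for baseline EQ-5D-5L utility, and incremental costs for baseline TiC-P costs, irrespective of observed baseline balance, with the adjustment repeated in each imputed data set and bootstrap replicate.

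Seemingly unrelated regression and the addition of the stratification factors are optional. It would also help to state whether QALY gains are the raw area or are baseline-subtracted.

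The cost is wording only. Baseline measurements already precede randomisation, so no visit, patient or extra time is needed. The change should be dated before any comparison of economic data by arm.

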### Interventions

#### rTMS

rTMS treatment will be performed using a Magstim Rapid 2 (Radboudumc) or a Deymed DuoMag XT-35 or XT-100 equipment (neurocare and ETZ) using generic figure-8 coils). All rTMS parameters used in the proposed study are within the range considered safe according to the latest published safety guidelines [34, 35]. Firstly, the resting motor threshold (rMT) will be defined in each participant as the minimal stimulation intensity evoking an MEP of ≥0.05 mV in 50% of the trials in the muscle of the right thumb (M. abductor pollicis brevis). Note that rMT will be determined at the beginning of every week before the first treatment session. We will use BeamF3 (freely available software at (http://clinicalresearcher.org/F3/calculate.php) to find the DLPFC, which is based on electrode position F3 from the EEG 10–20 system [36]. A detailed description of this method can be found in Beam et al., (2009) [36]. The coil will be positioned over this location at an angle of 45° relative to the midline.

rTMS will be conducted using a high-frequent protocol, applying 60 trains of 10 Hz pulses with a duration of 5 s and an inter-train interval of 25 s over the left DLPFC (50 pulses per train, 3000 pulses per session), with an intensity of 120% of the rMT. Twenty-five rTMS sessions will be given over the course of 8 weeks, following a schema of 4, 4, 4, 3, 3, 3, 2, 2 sessions per week. After a minimum of fifteen sessions (corresponding to 4 weeks), treatment may be ended. This is only possible when the scores on the HDRS-17 decrease to a minimum of symptoms (score < 8, in remission) for at least two measurements in a row. However, when the scores still show a decline, the patient is still improving and will likely progress even further. The rTMS sessions should be continued until the patient’s HDRS scores remain below 8 for two measurements in a row but no longer than 8 weeks (given the set-up of the approved ZonMW grant). Table 1 shows an overview of the rTMS treatments and measurements during the eight-week treatment period. Patients responding to rTMS are allowed to receive booster sessions in case of relapse.

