#### Medication

Treatment as usual will consist of protocolled pharmacological treatment steps that are prescribed within the medication algorithm of the Dutch guideline. This will consist of either a switch from the current antidepressant medication to a tricyclic antidepressant (TCA) or augmentation of the current antidepressant medication with lithium or a second generation antipsychotic [37]. Information on the type, dose and duration of medication will be recorded in Castor EDC.

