### Evaluation of treatment response and remission

One of our secondary outcomes is treatment response (50% reduction in HDRS-17 score) and remission (≤7 on HDRS-17) at 8 weeks, and 4 and 6 months. For a subgroup of patients, this data will also be available for 9 and 12 months, as part of the extended follow-up. For each treatment condition, the percentage of participants that responds or is in remission will be calculated, for each time point. Kaplan Meier survival estimates will be calculated based on outcome after the eight-week treatment period and during follow-up. Scores will be compared using Cox regression analysis to take into account both the rate of response or remission and the time needed to reach response or remission.

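### The value-for-money comparator is stated as medication alone, but that arm may receive rTMS after week 8, so the 6- and 12-month economic results compare two treatment strategies

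*Protocol article*

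**What the plan says.** All references are to the protocol article.

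- **Combining costs and effects** sets the decision question for the acceptability curve: whether "rTMS added to CBT and antidepressants offers good value for money relative to CBT and switching of antidepressants alone". The analysis is intention-to-treat, with multiple imputation.
- **Study design** states that medication-arm patients who "did not recover to the medication intervention can receive rTMS after completion of the first 8 weeks of treatment".
- **rTMS** (under Interventions) adds, for the other arm: "Patients responding to rTMS are allowed to receive booster sessions in case of relapse".
- **Medication** (under Interventions) defines the comparator drugs as a switch to a tricyclic or "augmentation of the current antidepressant medication with lithium or a second generation antipsychotic".
- **Effects** fixes the outcome of the cost-effectiveness analysis: "the central clinical end-term will be remission defined as a HDRS-17 depressive symptom severity of less than 8 at 6 months follow-up". Costs and QALYs are cumulated over follow-up, and a second analysis covers the subgroup followed to 12 months.
- **Costs** counts "healthcare costs including intervention costs (i.e. rTMS, pharmacotherapy, CBT sessions" among the items to be valued, so rTMS is costed.

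**The concern.** The economic question names a comparator without rTMS. The design provides such a comparator only up to week 8, while every economic outcome is measured or accumulated beyond that point. Under intention-to-treat, a medication-arm patient who later has rTMS stays in the medication arm, with the cost of the sessions and any benefit from them.

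The curve is meant for decision-makers. A conclusion written in the plan's words would claim good or poor value against a medication-only pathway that the trial does not test past week 8. Nothing elsewhere corrects this. Strengths and limitations does not mention delayed rTMS, and it promises information on cost-effectiveness over a longer course. Clinical implications presents rTMS as an alternative to antidepressant medication.

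**Working it through.** The sentence at issue contains no figure to reproduce. The check compares sections and then asks what the document allows one to say about size.

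**1. What each arm may receive**

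| Period | rTMS arm | Medication arm |
|---|---|---|
| To week 8 | rTMS, CBT, continued antidepressant | Switch or augmentation, CBT; no rTMS |
| After week 8 | Boosters allowed for responders who relapse | rTMS allowed if not recovered |

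The comparator named in Combining costs and effects, "relative to CBT and switching of antidepressants alone", matches the right-hand column in the first row only.

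**2. How much of each economic window lies after week 8**

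Inputs: 8 weeks of treatment (Study design), 6 months = 26 weeks, 12 months = 52 weeks.

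- 6 months: (26 − 8)/26 = 18/26 = 69%.
- 12 months: (52 − 8)/52 = 44/52 = 85%.

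These figures show how long the option is open. They are not uptake.

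**3. Whether a delayed course could affect the 6-month outcome**

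The rTMS section describes 15 sessions over 4 weeks as the minimum and 25 sessions over 8 weeks as the full course. Assume that a delayed course follows the same schedule and starts right after week 8. It then ends between week 8 + 4 = 12 and week 8 + 8 = 16. That is before the 4-month visit (about week 17) and well before month 6. A whole delayed course, with its costs and any benefit, can therefore fall inside the 6-month window.

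**4. Effect on the ICER**

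Let ΔC and ΔE be the incremental cost and effect against medication without any later rTMS. Let x and y be the mean net cost and mean net effect, per medication-arm patient, that delayed rTMS adds to that arm. The trial then estimates

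ICER = (ΔC − x)/(ΔE − y).

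With ΔC, ΔE, x, y and ΔE − y all positive, this is lower than ΔC/ΔE if x/y exceeds ΔC/ΔE, and higher if x/y is smaller. The document gives none of these quantities. Nor does it give the uptake of delayed rTMS or the criterion for not having recovered. At zero uptake, x = y = 0 and nothing changes. Neither size nor direction can be derived.

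**5. Primary analysis and sample size**

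The last primary HDRS-17 measurement falls in week 8, and rTMS opens to the medication arm only after those 8 weeks. The sample size concerns that 8-week outcome and reproduces:

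- variance factor (1 + 4 × 0.69)/5 − 0.59² = 0.752 − 0.3481 = 0.4039;
- n = 2 × (1.960 + 0.842)² × 0.4039/0.33² = 58.2, rounded up to 59 per arm;
- 59/0.90 = 65.6, rounded up to 66 per arm, or 132 in total.

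Neither is touched by this point.

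**The case against.** The best defence is that the sentence merely labels the randomized arms: one has rTMS added and the other does not. The later option is disclosed openly under Study design, the trial is called pragmatic, and rTMS is costed wherever it occurs. On this view the planned numbers already reflect the strategy contrast and only the label lags behind. Most of that stands, and it is why no analysis needs to change. It does not rescue the sentence, which states what the curve is meant to decide and says *alone*.

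A reader might infer more than the document supports:

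- **That the intention-to-treat ICER is biased or invalid.** It is a valid estimate of a pragmatic contrast between two strategies. Only the name given to the comparator is wrong.
- **That the comparator arm is misdefined because the sentence mentions only switching.** The abstract, Study design and Medication sections all include augmentation. The omission is loose wording, and nobody would drop augmented patients because of it.
- **That the section on response and remission is also wrong.** It reports outcomes "at 8 weeks, and 4 and 6 months" by treatment condition and never describes the comparator as medication alone. It needs no correction.
- **That delayed rTMS narrows the 6-month remission difference by some stated number of points.** Any such number would rest on assumed uptake, assumed eligibility and assumed benefit. The document supplies none of them.

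It can also be said that reporting of later rTMS belongs in the full protocol or analysis plan, which is not shown. That is fair, and its absence from the article is no fault. It appears below only because the restated comparator cannot be interpreted without it.

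**Conclusion.** The point holds as a mis-stated decision comparator. Beyond week 8, the economic analysis compares *rTMS now, boosters allowed on relapse* with *next medication step plus CBT first, rTMS available after week 8 if not recovered*. It does not compare rTMS with medication alone.

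This rests on the text and needs no assumption about uptake. The mismatch can operate over 69% of the 6-month window and 85% of the 12-month window, but its numerical effect on the ICER is unknown in size and direction. It should be fixed because it changes what decision-makers may conclude. Design, intention-to-treat analysis, ICER computation, primary analysis and sample size all stand.

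**What to change.** Keep the delayed-rTMS option, the intention-to-treat analysis and the ICER computation.

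1. Reword the decision question under Combining costs and effects along these lines: *whether starting rTMS now, with CBT and continued antidepressants and with boosters allowed on relapse, offers good value for money relative to CBT with the next medication step (switch or augmentation) first and rTMS available after week 8 if not recovered.*
2. Limit value-for-money conclusions at 6 and 12 months to that contrast. Draw conclusions about rTMS versus medication without rTMS from the week-8 outcome only.
3. Report the number of patients and sessions of delayed rTMS in the medication arm, and of boosters in the rTMS arm.

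The cost is one reworded sentence, a limit on how later results are described, and a row in a descriptive table. Costing rTMS needs the session counts anyway.
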